### Ethical consideration

This study complies with the international ethical guidelines for a clinical study. Ethical approval has been obtained from the Human Research Ethics Committee of the University of the Witwatersrand (M130113). Patients will be required to read and sign informed consent, and revocation of consent will not detriment the patients in any way.

### Trial registration

This study has been registered with the Pan African Clinical Trial Registry and has the trial number PACTR201405000823418 (http://www.pactr.org).

### Intervention and control

All vibration training will be performed on standard power plates (DKN XG 5.0, DKN Technology, California, USA) under the supervision of the primary investigator. Vibration training will consist of 24 total sessions (performed twice weekly for 12 weeks); in intermittent bouts of 60 seconds on the plate and 30 seconds off the plate, repeated 10 times (this protocol was designed to stimulate greater osteogenic responses due to the constant stimulus to the mechanoreceptors [27]). Patients will be required to stand on the plates, barefoot and with knees slightly bent, holding firmly to the bars. Vibration plates will be set at a constant frequency of 30Hz and amplitude of 3 mm in order to maximize the osteogenic and muscle activation effects of the therapy [27]. The CON group will continue to receive standard care for the intervention period, and will be instructed to continue with their normal daily activities for the three month period.

### Sample size

A sample size calculation (ß = 0.10) based on detecting a minimum clinically important difference of 0.22 in HAQ score (using an SD of 0.19) [36] between the two groups, showed that at a 5% level we would require a sample of 8 participants in each group with a power of 90%.

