**Flow diagram of study design.**

### Participants

Fifty participants will be recruited from the Rheumatology Clinic at the Chris Hani Baragwanath Academic Hospital in Soweto, South Africa. Recruitment will include the outpatients attending the clinic at the quarterly check-up via a brief interview following dissemination of study information. Consenting patients will be included if they are older than 18 years, have been diagnosed with RA (according to the 1987 ACR criteria [35]) at least three years previously, are on stable drug therapy (prednisone <10 mg/day), and had been for at least three months previously. Patients will be excluded if they are HIV+, are using bisphosphonates or corticosteroids, have any co-morbidities that could potentially impact on physical activity levels, are using assistive walking devices, have previously had hip or knee joint replacement surgery, and if they are pregnant.

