### Statistical analysis

Statistical analysis will be carried out using Stata version 12/IC 12.0. All data will be presented as mean ± SD, and a p value ≤0.05 will be considered significant. Data will be analysed on an intention to treat basis. Student’s unpaired t-tests will be used to compare absolute, as well as change in HAQ, BMD, physical activity, patient characteristics, and RA disease activity data between the WBV group and CON group at baseline. Cohen’s D effect sizes will be calculated to determine the magnitude of effects observed.

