### Potential obstacles

Potential obstacles include adherence to the protocol, and attempting to minimise the attrition rate of the study. Participants will be in regular contact with the primary investigator who will attempt to minimise attrition, as well as follow up on patient’s health on a weekly basis. The short duration of the study, as well as the intermittent design of the study, lead us to expect an attrition rate of approximately 20% according to a meta-analysis by Linke et al. in 2009 [43]. There is the potential that WBV may cause adverse effects or may not be tolerated in some participants; however the primary investigator will observe every WBV session, and assess pain levels at each WBV session in order to monitor this. It is also possible that WBV will have no effect on the outcomes measured.

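### The stated 8 per group does not follow from the protocol's own inputs: 90% power needs 17 per group, and 8 per group gives about 58%

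*Protocol article*

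**What the plan says.** The Sample size section of the protocol article bases the calculation on "detecting a minimum clinically important difference of 0.22 in HAQ score". The spread is entered as "using an SD of 0.19", and beta is set at 0.10. The comparison is explicitly one of two arms at a 5% level, and the conclusion drawn is that "we would require a sample of 8 participants in each group with a power of 90" per cent. The section does not say whether the 5% level is one- or two-sided, or whether 0.19 is the SD of the HAQ score or of its change.

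Three other places bear on the number:

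- Participants: "Fifty participants will be recruited from the Rheumatology Clinic".
- Potential obstacles: the study's features "lead us to expect an attrition rate of approximately 20" per cent.
- Statistical analysis: "Student’s unpaired t-tests will be used to compare absolute, as well as change in HAQ", along with other outcomes. No pairing, baseline adjustment or other variance reduction is described.

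The Sample size section mentions neither the 50 patients nor the attrition.

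**The concern.** A difference of 0.22 with an SD of 0.19 is a standardised effect of 0.22/0.19 = 1.16. That is large, but 8 per arm is still too few to detect it with 90% power when two independent groups are compared. The figure looks like the answer to a one-sample problem.

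This is the only justification given for the size of the trial on its primary outcome. If 8 per group is taken as the number needed, the 20 per group expected to remain after attrition look like two and a half times the requirement, and heavy losses would seem harmless. If the true requirement is 17, the margin is three patients per group.

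**Working it through.** **Inputs**

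| Input | Value | Source |
|---|---|---|
| Difference δ | 0.22 | Sample size |
| SD σ | 0.19 | Sample size |
| Level | 5%, taken as two-sided (assumption), z = 1.960 | Sample size |
| Power | 90%, z = 1.282 | Sample size |
| Test | unpaired t-test | Statistical analysis |
| Allocation | alternating, so 1:1 | Study design |
| Recruitment | 50, so 25 per group | Participants |
| Attrition | 20% | Potential obstacles |

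**Step 1: reproduce the stated figure.** Without the factor of 2,

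n = (1.960 + 1.282)² × (0.19/0.22)² = 10.507 × 0.7459 = 7.84, rounded up to 8.

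This is the stated number. It is the formula for one mean against a fixed value.

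**Step 2: the two-group formula.** The variance of a difference between two independent means is 2σ²/n, so

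n per group = 2 × 7.84 = 15.67, rounded up to 16.

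**Step 3: the planned test.** Power from the noncentral t distribution, with 2n − 2 degrees of freedom and noncentrality δ/(σ√(2/n)):

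| n per group | Power, two-sided 5% |
|---|---|
| 8 | 57.8% |
| 16 | 88.7% |
| 17 | 90.5% |
| 20 | 94.6% |
| 25 | 98.0% |

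So 17 per group is the smallest number that reaches 90%. At n = 8 the noncentrality is 0.22/(0.19 × 0.5) = 2.32. The normal approximation there gives Φ(2.316 − 1.960) = 63.9%.

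**Step 4: other readings of the inputs** (normal approximation, two groups)

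| Reading | n per group |
|---|---|
| One-sided 5%, 90% power | 12.8, so 13 |
| Two-sided 5%, 80% power | 11.7, so 12 |
| One-sided 5%, 80% power | 9.2, so 10 |

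None gives 8, and the last two contradict the stated 90%. If the test were one-sided, power at 8 per group would be 71.1% (t-test).

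**Step 5: link to recruitment.** Allowing for 20% attrition, 17/0.8 = 21.25, so 22 per group or 44 in all. The 50 planned exceed this. With 25 × 0.8 = 20 per group evaluable, power is 94.6%.

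**Step 6: the real margin.** With 20 per group, power stays at 90% up to an SD of about 0.209 (92.4% at 0.20, 89.8% at 0.21). At SDs of 0.30 and 0.40, which are illustrative and not from the document, it is 62% and 40%.

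**The case against.** The strongest reply is that nothing the trial will do depends on the figure. It plans to recruit 50 patients, not 16. On its own inputs that gives 98.0% power with everyone evaluable and 94.6% after the expected attrition. Falling from 25 to 8 per group would take a loss of 17/25 = 68%, and the article describes no interim look or early stopping. This stands, and it confines the error to the justification.

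The cause is also inferred, since the article prints no formula. An unstated variance reduction could give a similar number: baseline adjustment with a correlation of 0.7 gives 15.67 × (1 − 0.49) = 7.99. The caution about cause is fair, but it does not rescue the figure, because the article describes no adjustment and plans unpaired t-tests.

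It can be added that an article may condense the reason for recruiting 50, and that recruiting above a calculated minimum contradicts nothing. That is also fair. The missing link to the 50 would be no error by itself. Likewise, the SDs of 0.30 and 0.40 are assumptions about a separate question and do not carry the point.

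What remains is a printed answer that contradicts its printed inputs. A fuller protocol or an analysis plan cannot make that sentence correct.

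**Conclusion.** The point holds. On the stated inputs the requirement is 16 per group by the normal approximation and 17 by the t-test that is planned, so 8 is about half of what is needed. At 8 per group the type II error is about 42%, against the stated 10%.

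This rests on a two-sided 5% test, equal groups and 0.19 being the SD of the quantity compared. A one-sided test reduces the discrepancy but does not remove it. Whether 0.19 refers to the score or to its change makes no difference to the need for the factor of 2. That the factor was omitted is an inference from an exact numerical match; that the result is wrong is not an inference.

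No more patients are needed at SD 0.19. The statement of sample size and power for the primary outcome must still be corrected, because it is wrong by the plan's own figures and overstates the room for losses.

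**What to change.** Replace the sample size sentence with wording to this effect: 17 evaluable patients per group give 90% power to detect a HAQ difference of 0.22 between groups (SD 0.19, two-sided 5% level, unpaired t-test); allowing for 20% attrition, at least 22 per group must be enrolled; the 50 planned give about 95% power with 20 evaluable per group.

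It would also help, though the correction does not depend on it, to say whether 0.19 is the SD of the HAQ score or of its change, and to give the power at one or two larger SDs.

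The cost is rewording only. Recruitment, design and analysis do not change.

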### Outcome measures

All outcomes will be measured at baseline, and reassessed after the three month intervention, as well as again three months post intervention. The primary outcome of this study will be an improvement in functional ability as assessed by the HAQ. The secondary outcomes will be attenuation in loss of BMD at the hip, as well as improvements in subjective pain scores, SF-36, CDAI, and objective habitual physical activity levels (Table 1).

**Table 1 Tab1:** **Summary of outcome measures and respective methodology**

Outcome		Measurement method	Time point (months)
**Primary**	Functional ability	Health assessment questionnaire	0,3,6
**Secondary**	BMD	DXA	0,3,6
	Habitual physical activity	Accelerometry (Actical worn on the hip)	0,3,6
	Disease activity	CDAI assessment	0,3,6
	Pain	Self reported via Lickert scales	0,3,6 as well as at each session of WBV therapy
	Fatigue	Self reported via Lickert scales	0,3,6
	Body composition and anthropometry	DXA, standard scale, and stadiometer	0,3,6
	Acute inflammation	CRP	0,3,6

### Primary

#### Functional ability

Patients will be asked to complete the modified Health Assessment Questionnaire (HAQ) [37], which is a RA specific questionnaire that assesses functional ability by providing a score of functionality between 0 and 3, where 0 indicates good functionality and 3 indicates severe functional disability.

### Secondary

The secondary outcomes of the study are attenuation in loss of BMD, as well as any improvements in HRQoL, disease activity, habitual physical activity or body composition measurements. These will be assessed as follows:

#### BMD

All patients will be assessed, for site specific areal BMD at the left hip, lumbar spine (L1-L4), and whole body using Dual X-Ray Absorbtiometry (DXA). T and Z scores will then be calculated according to reference values. All scans will be performed by the same qualified technician on the same machine (Hologic QDR 4500A, Hologic, Boston, USA). The machine is routinely calibrated, and a phantom spine will be scanned daily to determine coefficients of variation of the machine. The technician will be blinded as to the grouping of participants during the study. According to previous studies examining bone loss over time in age matched female patients with RA [38], and the effects of exercise interventions on this type of bone loss [39]; we expect a decrease of approximately 0.33% in hip BMD in the control group, and for this loss to at least be attenuated in the WBV group.

#### Physical activity

At the first assessment, during the last week of the intervention, and again at the follow up assessment, patients will be fitted with an Actical (Respironics Inc., Murrysville, PA, USA) accelerometer (for the assessment of habitual physical activity) worn on a Velcro belt on the hip for a one week period. Patients will be instructed to wear the accelerometer all day, and to remove the device only while sleeping, bathing or showering. Patients will then return the accelerometer to the clinic one week later. Actical data are reported in one minute epochs and raw data are reduced by removing full days of non-wear time by visual inspection of the data where a full day of consecutive zero activity counts are observed. Sleep time is also removed by visual inspection of the data, and the remaining data will be considered as wear time. Thereafter, a valid day will require at least ten hours of wear time per day, and at least four valid days will be required for inclusion in the final analysis [40]. Data will be reported as average activity counts per day, as well as percentage of time spent in sedentary, light, moderate and vigorous activity thresholds, as calculated by the inbuilt algorithm on the Actical software. The number of bouts of activity, as well as the number of breaks in sedentary activity per day will also be reported, the methodology of which has been explained previously [41]. Participants will be fitted with the same Actical at each visit in order to minimise inter-device variability. This will allow for the assessment of habitual physical activity patterns before and after the intervention.

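### The month-3 accelerometer week can overlap the last WBV sessions, so the contrast in habitual activity may partly record attendance in one arm

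*Protocol article*

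**What the plan says.** The Physical activity section fits the device at the first assessment and then "during the last week of the intervention, and again at the follow up assessment, patients will be fitted with an Actical". It is "worn on a Velcro belt on the hip for a one week period", and patients are told to "remove the device only while sleeping, bathing or showering"; WBV sessions are not among the exceptions.

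Data reduction is specified. Full days without wear are dropped. Then: "Sleep time is also removed by visual inspection of the data, and the remaining data will be considered as wear time". On validity, "a valid day will require at least ten hours of wear time per day, and at least four valid days will be required". The section closes: "This will allow for the assessment of habitual physical activity patterns before and after the intervention".

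The Outcome measures section gives one timing rule for everything: "All outcomes will be measured at baseline, and reassessed after the three month intervention". Table 1 lists accelerometry at months 0, 3 and 6.

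The Intervention and control section schedules 24 supervised WBV sessions, two a week over 12 weeks, each of ten cycles of 60 seconds on and 30 seconds off the plate. Controls have standard care and their usual activities, with no comparable visits.

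**The concern.** The outcome is habitual activity. A scheduled visit that exists in one arm only, and stops when the intervention stops, is not habit. If the wear week overlaps week 12, the WBV record can contain up to two such visits and the control record none, and no stated step takes them out.

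Three uses of the data are exposed:

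- **The month-3 comparison.** Part of any difference in counts, time by intensity, activity bouts or breaks in sedentary time could come from attending.
- **Sustainability.** The Discussion relies on the post-intervention visit to judge whether changes last. Attendance disappears between month 3 and month 6, so a fall in the WBV arm could partly be the end of the visits.
- **Interpretation.** The Discussion suggests that increased activity might help explain changes in function and BMD, and describes these patients as very sedentary. Small additions to active time could then be over-read.

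The document also disagrees with itself on whether month 3 is an on-treatment or a post-treatment measurement.

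**Working it through.** There is no stated figure to reproduce. The check is of timing, then of how much session time the record could hold.

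**Inputs (protocol article)**

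- Sessions: 24 over 12 weeks (Intervention and control).
- Session: 10 cycles of 60 s on and 30 s off (same section).
- Wear period: one week, fitted at an unspecified point in the last intervention week (Physical activity).
- Valid record: at least 4 days of at least 10 h (Physical activity).
- Plate frequency: 30 Hz (Intervention and control). Device detection band: 0.5 to 3.2 Hz (Background).

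**Overlap**

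Sessions per week = 24 / 12 = 2, so week 12 still contains two. If the device is fitted before both, the wear week holds 2 sessions; between them, 1; after both, 0. The overlap is therefore 0 to 2 sessions and could differ between WBV patients. At most, session days are 2 of 7 recorded days (29%), or 2 of 4 (50%) in a minimally valid record that happens to include both.

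**Session time as a share of wear time**

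Session length = 10 × (60 + 30) s = 900 s = 15 min, of which 10 min are on the plate.

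Share = (sessions × 15) / (valid days × 10 × 60).

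| Sessions in wear week | Minutes | 7 days × 10 h = 4,200 min | 4 days × 10 h = 2,400 min |
|---|---|---|---|
| 0 | 0 | 0% | 0% |
| 1 | 15 | 0.36% | 0.625% |
| 2 | 30 | 0.71% | 1.25% |

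With two sessions this is 30 / 7 = 4.3 to 30 / 4 = 7.5 min per valid day. Ten hours is the minimum for a valid day, so longer wear makes the shares smaller.

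**Attendance and travel (assumption only)**

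Venue, distance and mode of travel are not given. If each session brought a further 60 to 120 min of travel, two sessions would occupy 2 × (15 + 60) = 150 to 2 × (15 + 120) = 270 min. That is 3.6% to 6.4% of 4,200 min, or 6.25% to 11.25% of 2,400 min. This is time occupied, not activity added: some of it may be seated, and it may displace other activity.

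**What the device would register**

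30 Hz lies well above the stated band, so the vibration itself may add few counts. Walking, standing and stepping on and off the plate are the likelier contributors.

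**After the fix**

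If the wear week starts after the last session, or if session and attendance time are cut from both counts and wear time, the contribution is 0 min.

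**The case against.** The strongest reply is that an on-treatment measure may be intended. The Discussion says that accelerometry will describe changes arising both in the course of the intervention and after it. A recording in week 12 would supply the first and month 6 the second, so the conflict with the Outcome measures section could be loose wording about a month-3 visit. This stands in part. The Discussion supports either reading, but the Outcome measures section and the closing sentence of Physical activity both point to a post-treatment measurement. Even an on-treatment measure of habit needs session time separated out.

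A second reply is that handling of session time is a detail that a condensed article leaves to the full protocol or analysis plan. That would be fair if the article were silent. It is not: it lists what is removed and declares everything left to be wear time.

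A reader might go further and infer that the design builds in a known bias in favour of WBV, with two of every seven recorded days affected. The document does not support that. The fitting day is not fixed, so two sessions is a ceiling. The vibration is outside the detection band. Patients stand still holding the bars, and travel may be seated. Any estimate in percentage points beyond the session itself needs attendance times that the article does not give.

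**Conclusion.** The concern holds in limited form. As written, the month-3 measure of habitual activity is not comparable between arms, because the WBV record may contain up to two supervised sessions and the control record none, and the stated data reduction keeps that time. The month-3 to month-6 change is affected in the same way. The timing contradicts the Outcome measures section and the before-and-after purpose stated under Physical activity, although the Discussion also mentions changes while treatment is under way.

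The supported size is 0 to 30 min of session time in the wear week: up to about 0.7% of a 7 × 10 h record and 1.25% of a 4 × 10 h record. Anything larger rests on assumed attendance and travel time. An upward bias for WBV is the more plausible direction, but it is not established. The outcome is secondary and the HAQ comparison is untouched, but the correction is cheap and should be made before recording starts.

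**What to change.** - Start the month-3 wear week after the final WBV session, and at the matching time from enrolment in controls. State the fitting day relative to that session.
- Make sure that the baseline wear week ends before the first WBV session; starting it before that session is not enough.
- Align the Physical activity and Outcome measures sections, and the Discussion, on whether month 3 is on-treatment or post-treatment.
- If an on-treatment measure is wanted, say so. Log session and attendance times and remove that time from both counts and wear time by a rule fixed in advance. Do not drop whole session days in the WBV arm only: that shortens the records of one arm, makes the sampled days differ between arms and risks failing the four-day requirement.

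Cost: one trip to return the device a week after the month-3 assessment, as already happens at the other visits, and a measure taken just after treatment rather than during it. The logging option avoids the second cost but adds record keeping.

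### The accelerometer rule counts non-wear in the middle of a day as wear, which overstates sedentary time and stops the ten-hour test from rejecting days with long gaps.

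*Protocol article*

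**What the plan says.** The Physical activity section of the protocol article gives an ordered data-reduction rule for the one-week recordings.

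- Wearing instruction: patients are "to remove the device only while sleeping, bathing or showering", so a little waking non-wear is expected by design.
- Resolution: "Actical data are reported in one minute epochs".
- Step 1, non-wear: this step consists of "removing full days of non-wear time by visual inspection of the data where a full day of consecutive zero activity counts are observed".
- Steps 2 and 3, sleep and the definition of wear: "Sleep time is also removed by visual inspection of the data, and the remaining data will be considered as wear time".
- Step 4, validity: "Thereafter, a valid day will require at least ten hours of wear time per day, and at least four valid days will be required".
- Reported measures: "Data will be reported as average activity counts per day, as well as percentage of time spent in sedentary, light, moderate and vigorous activity thresholds". In addition, "The number of bouts of activity, as well as the number of breaks in sedentary activity per day will also be reported".

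Table 1 lists habitual physical activity as a secondary outcome at 0, 3 and 6 months.

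**The concern.** Step 3 is a positive definition: whatever is left after whole zero days and sleep is wear. No earlier step takes out non-wear within a day. If the belt comes off for part of an afternoon and goes back on, the zeros in between are treated as minutes of wear without movement.

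Two things follow. The gap enlarges the denominator and the sedentary numerator together, so the sedentary percentage rises and the other bands fall. And because validity is tested on credited rather than actual wear, the ten-hour threshold cannot exclude a day with a long gap, which is what such a threshold is for.

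At stake is the interpretation of an outcome that the Discussion presents as a main advantage of the trial: a detailed and accurate account of how activity patterns change.

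**Working it through.** The plan gives no figure to reproduce here, so the check works the written rule through.

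**Inputs from the document:** the order of the four steps, the ten-hour threshold and the one-minute epochs.

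**Assumptions, because the document gives no values:** credited waking day D = 24 h minus the time cut as sleep. The base case is 8 h cut, so D = 16 h; the range is 7 to 10 h cut, so D = 17 to 14 h. True sedentary share while worn s = 70% (range 60 to 80%). The gap of g hours lies mid-day, with wear on both sides. Zero counts fall in the sedentary band; the cut-point is left to the Actical software, but zero is the lowest possible count.

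**Validity test.** For a full recorded day with any non-zero count, credited wear is D whatever the gap. The day fails only if D < 10 h, that is, if more than 14 h is cut as sleep. With 8 h cut, a day really worn for 8 h is credited 16 h and passes.

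**Sedentary share.** With actual wear w = D − g:

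apparent share = (s × w + g) / D, so overstatement = g × (1 − s) / D.

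Base case, D = 16 and s = 0.70:

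- g = 0.5 h: (0.70 × 15.5 + 0.5)/16 = 70.9%
- g = 2 h: (0.70 × 14 + 2)/16 = 73.75%
- g = 4 h: (0.70 × 12 + 4)/16 = 77.5%
- g = 8 h: (0.70 × 8 + 8)/16 = 85.0%

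The range below runs from g × 0.20/17 to g × 0.40/14.

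| Mid-day gap | Really worn (base) | Credited (base) | Passes as written | Would pass on actual wear | Overstatement, base | Overstatement, range |
|---|---|---|---|---|---|---|
| 0.5 h | 15.5 h | 16 h | yes | yes | 0.9 points | 0.6 to 1.4 |
| 2 h | 14 h | 16 h | yes | yes | 3.75 points | 2.4 to 5.7 |
| 4 h | 12 h | 16 h | yes | yes | 7.5 points | 4.7 to 11.4 |
| 8 h | 8 h | 16 h | yes | no | 15.0 points | 9.4 to 22.9 |

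**Comparisons.** If both groups have the same gap, a true difference in s is multiplied by (1 − g/D): 0.875 for a 2 h gap and 0.75 for a 4 h gap. If gaps differ, for instance 2 h at one visit and 4 h at another with identical behaviour, the rule produces 77.5 − 73.75 = 3.75 points of apparent change.

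**Other measures.** A gap appears as one unbroken sedentary stretch, which distorts bouts and breaks. Zeros add nothing to a day's total counts, so average counts per day change only because poorly worn days are kept.

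**The case against.** The strongest reply is that the rule catches more than its wording suggests. The belt is off at night, so sleep is also recorded as zeros, and someone reading the trace would probably cut a late start or an early removal together with the night. Such a day can then fail the ten-hour test, as can part-days at fitting and return. This stands, and it confines the point to mid-day gaps. A reader might infer that the ten-hour rule screens out almost nothing; the text does not support that.

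Second, the only waking removal the protocol permits is for washing, and a 30-minute gap costs under 1 point in the base case. Large errors need patients to depart from the wearing instruction. That also stands. The document gives no wear data, so how often long gaps occur is unknown.

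Third, a reader might infer a spurious benefit for WBV, on the argument that patients seen twice weekly wear the belt more faithfully at month 3. The document does not establish this. Its Potential obstacles section describes regular contact and weekly follow-up by the primary investigator without limiting them to the WBV group, and no WBV sessions take place around the baseline or month-6 recordings.

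Fourth, the section does not say whether the person reading the traces is blind to group. That is a detail an article may leave to the full protocol, so it is not part of this point.

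Finally, deleting zero runs in very sedentary patients risks deleting real sitting. That is a fair limit on the remedy, and the reason for a second, longer window.

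None of this removes the core problem. The text defines the remaining minutes as wear and only then applies the validity test, so a mid-day gap counts as sedentary wear.

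**Conclusion.** The concern holds for non-wear in the middle of a day. Followed as written, the rule overstates the sedentary share by g × (1 − s)/D and leaves the ten-hour test unable to reject days with long mid-day gaps. The error is about 1 point for a washing-length gap, 3.75 points for 2 h and 7.5 points for 4 h. For 8 h it is 15 points, on a day that falls short of the plan's own threshold. These sizes rest on an assumed 16 h waking day and a 70% true sedentary share; the ranges are in the working.

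With equal wear in both groups, the effect is a raised sedentary level and a diluted contrast, not an invented treatment effect. A between-group bias arises only if wear differs by group, and that remains an assumption. The outcome is secondary and the HAQ analysis is unaffected. The rule should be changed, but it does not threaten the trial's main conclusion.

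**What to change.** Before the ten-hour and four-day test, remove within-day non-wear by a fixed, scripted rule applied identically to all files: for example, any run of at least 60 consecutive zero-count minutes in waking time. Define wear time as what remains, and test validity on that. Because these patients are very sedentary, repeat the analysis with a longer window such as 90 minutes. Both windows are illustrations, not values from the document; what matters is that they are fixed in advance.

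The rule runs on the one-minute data already planned, with no extra visits or measurements. The costs are that some motionless sitting is classed as non-wear and a few more days, possibly a few patients, drop out of this analysis. Gaps shorter than the window stay in; for a 30-minute gap that leaves about 0.9 points in the base case.
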